### Sample size estimation

No published study to date has compared the treatment effects of cognitive training, physical exercise training, sequential training, and dual-task training in older adults with MCI. Therefore, we estimated the sample size for the current study from the studies that compared sequential training or dual-task training with control intervention(s) in older adults with cognitive complaints [15–17]. Because our primary outcomes will include global cognitive function and executive function, we calculated the sample sizes on the outcomes that involve these cognitive aspects. Kounti et al. [16] found significant benefits of dual-task training on global cognitive function, as measured by the Mini-Mental State Examination (MMSE), in participants with MCI. Compared with the control intervention, the calculated effect size (Cohen’s *d*) was 0.63 for dual-task training [16]. Using G*Power software [30] with a power of 0.80 and a two-sided type I error of 0.05, the calculated total sample size for the current study will be 20 participants (i.e., 5 participants in each group). The study conducted by Suzuki et al. showed that compared with the control group, the multicomponent dual-task training group had greater improvement in MMSE after intervention [17]. Based on the calculated effect size for the MMSE (Cohen’s *d* = 0.45), we estimated the sample size for the current study will be 12 participants in each group. Barnes et al. investigated the treatment effects of a sequential combination of physical exercise and mental activity training and found significant benefits on the Useful Field of View (UFoV), a measure of executive function, in older adults with cognitive complaints [15]. We used the calculated effect size for the UFoV from Barnes’ study (Cohen’s *d* = 0.21) [15] to estimate a sample size of 32 participants in each group.

Similar to the study design conducted by Barnes et al. [15], we employ the active control groups (i.e., COG and PE groups) instead of a no-treatment or passive control group. On the other hand, the primary outcome measures used in the current study are closer to those used by Kounti et al. [16] and Suzuki et al. [17]. Hence, a mean value from the estimated sample sizes of the three studies was calculated, and we anticipated that recruiting 16 participants for each group should be sufficient for this proposed study.

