The dropout rate in our pilot trial was approximately 20 % during the intervention period; hence, we plan to recruit 20 participants for each group resulting in a total sample size of 80 patients for four groups.

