### Study design and procedures

This proposed study is a randomized controlled trial with pretest, posttest, and 6-month follow-up assessments (Fig. 1). The study protocol is approved by the Chang Gung University Institutional Review Board. Intervention therapists will screen for potential participants and obtain signed informed consents from the eligible individuals before they participate in the study. The enrolled participants will be randomly assigned into the COG, PE, SEQ, or DUAL group with the allocation ratio of 1:1:1:1 [31]. Random tables based on the type of recruitment site (day care centers versus nursing homes versus community) will be generated by an independent research assistant using the web-based Research Randomizer tool (freely available at http://www.randomizer.org/) [32]. The research assistant will use the random table to decide the group allocation of a newly enrolled participant and will inform the relevant therapist to carry out the respective intervention. The intervention therapist will not know the group allocation until the pretest measurement is completed. Each intervention group will consist of three to five participants and will be guided by a trained therapist. The participants will engage in 90 min of training, two to three times a week, for a total of 36 training sessions.

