### Data analysis

We will use analysis of variance (ANOVA) and χ^2^ to analyze differences in baseline characteristics and baseline outcome measures among the groups. Any differences among the groups in the baseline sociodemographic variables will become covariates in the subsequent statistical analysis. Repeated measures ANOVA will be used to determine the intervention effects for the four groups. A significant statistical level will be set at 0.05 for all comparisons. Besides *p* values, effect size η^2^ will also be calculated to determine the group difference for each outcome measure. An η^2^ greater than 0.138 is considered to be a large effect, an η^2^ between 0.138 and 0.059 is a moderate effect, and an η^2^ between 0.01 and 0.059 is a small effect [58]. Intention-to-treat will be used for missing data. Data analysis will be performed with PASW Statistics 18.0 software (IBM Corp., Armonk, NY, USA).

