This study is distinctive for comparing the treatment effects of various dose-matched interventions in older adults with MCI. Schaefer and Schumacher emphasized the importance of equal treatment time when designing a randomized controlled trial for older individuals with MCI [59]. This study has, therefore, designed a comprehensive assessment and intervention protocol to investigate the treatment effects of different combined therapies in people with MCI.

One big challenge that we may encounter for the study is the difficulty in recruiting participants and another is the ability to maintain those participants. Recruiting older adults who have some cognitive impairment, but do not have other neurologic or psychological disorders, could be very challenging. Those older individuals typically stay in their home community and maintain a fairly active life before they become too old to carry out household tasks. To address this problem, we will target older adults who are sent to community day care centers and some nursing homes that admit older individuals without caregivers. Furthermore, the older adults who agree to participate in the study may decide to discontinue from the program during the 36 training sessions. Dropping out of the intervention program may be due to personal reasons (e.g., falls, diseases, or low motivation) or family issues (e.g., moving, need to take care of their partner, or change in caregivers) that may prohibit them from continuing the study. We accounted for the dropout rate in the sample size estimation to ensure that we could reach sufficient power for the study.

The overall goal of this study is to compare the treatment effects of different combinations of physical exercise and cognitive training. The results of this study will be important for clinicians as well as family caregivers to select the most efficient and effective training approach to improve cognitive, physical, and daily functions in older individuals with MCI. Most importantly, the ultimate goal of these interventions is to enhance their ability to live independently and to improve their quality of life.

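### The dropout allowance is used up by posttest, so 16 per arm with all three visits is unsupported at the 6-month follow-up

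*Protocol article*

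**What the plan says.** All passages are in the protocol article.

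- **Sample size estimation.** Sizes of 5, 12 and 32 per group are derived from three published studies "with a power of 0.80 and a two-sided type I error of 0.05". Their mean is taken as 16 per group and judged sufficient. The inflation step follows: pilot dropout was about 20% "during the intervention period; hence, we plan to recruit 20 participants for each group", giving 80 in total.
- **Study design and procedures.** The trial is a "randomized controlled trial with pretest, posttest, and 6-month follow-up assessments".
- **Data analysis.** "Repeated measures ANOVA will be used to determine the intervention effects for the four groups". The visits that enter the model are not listed. Intention-to-treat is named as the approach to missing data, without a method.
- **Discussion.** After describing people who leave during the 36 sessions, the article says: "We accounted for the dropout rate in the sample size estimation to ensure that we could reach sufficient power for the study".

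No section gives an expected loss between posttest and the 6-month visit, and none names the time point to which the sample size applies.

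**The concern.** The allowance covers a shorter period than the trial observes. Thirty-six sessions at two to three per week take 12 to 18 weeks; the follow-up then runs for 6 months, about 26 weeks. The reasons for dropout listed in the Discussion (falls, disease, moving, a change of caregiver) do not end with the last session.

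A standard repeated measures ANOVA uses only participants with a value at every visit entered. If all three visits are entered and gaps are not filled in, a participant with a valid posttest but no 6-month visit is lost from the whole analysis, including the posttest contrast. That costs precision, and it can bias the comparison if loss is related to outcome and arm. The reassurance about power in the Discussion does not warn the reader that nothing was set aside for this period.

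**Working it through.** **1. The plan's own figure.**
Mean of the three sizes: (5 + 12 + 32)/3 = 16.33, taken as 16.
Inflation for 20% loss: 16/(1 − 0.20) = 20 per arm; 4 × 20 = 80. The stated target is reproduced from 16 onwards. (The 5, 12 and 32 themselves were not reproduced together under any single setting tried; this point does not depend on them.)

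**2. What is left after posttest.**
20 × (1 − 0.20) = 16.0 per arm at posttest, so the reserve for later loss is zero.

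**3. Participants with all three visits.**
Let L be the share of those reaching posttest who miss the 6-month visit. The documents do not give L; the range is assumed. The number with all visits is 16 × (1 − L).

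**4. Power under complete-case repeated measures ANOVA.**
Group-by-visit test, k = 4 groups, m = 3 visits, alpha 0.05, N = 4 × number per arm. Noncentrality λ = f² × N × m/(1 − ρ), with df1 = (k − 1)(m − 1) = 6 and df2 = (N − k)(m − 1). The effect f is set so that power is 0.80 at 16 per arm (N = 64, df2 = 120): f = 0.193 if ρ = 0.5 and f = 0.150 if ρ = 0.7. Both give λ = 14.35, so the power column is the same for either ρ.

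| L (assumed) | Per arm with all visits | λ | Power |
|---|---|---|---|
| 0% | 16.0 | 14.35 | 0.80 |
| 5% | 15.2 | 13.63 | 0.77 |
| 10% | 14.4 | 12.92 | 0.75 |
| 15% | 13.6 | 12.20 | 0.71 |
| 20% | 12.8 | 11.48 | 0.68 |

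This f is a benchmark for relative loss. It is not one of the protocol's effect sizes, because 16 is an average and not the size that gives 0.80 for any of them.

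**5. Check against the protocol's own sizes.**
- Effect size that "was 0.63 for dual-task training" ("i.e., 5 participants in each group"): met at 16 and at 12.8.
- Effect size "0.45), we estimated the sample size for the current study will be 12 participants in each group": met at 16 and at 12.8; it fails only when L exceeds 25% (16 × 0.75 = 12).
- Effect size 0.21, 32 per group: missed at 16 with no follow-up loss at all.

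As an illustration with f = d/2, ρ = 0.5 and three visits (all assumed), going from 16 to 12.8 per arm moves power from 0.999 to 0.991 (d = 0.63), 0.918 to 0.830 (d = 0.45) and 0.271 to 0.217 (d = 0.21). No result crosses 0.80.

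**The case against.** **Missing data.** The Data analysis section states intention-to-treat for missing data, which signals an intent to keep participants. If missing visits were filled in, nobody would leave the ANOVA and the reduced numbers in the table would not arise. This stands in part. No method is named, so complete-case exclusion is what the named analysis does by default, but it cannot be presented as what will happen.

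**Time point.** The article does not say that the size was set for 6 months or which visits the model includes. If it was set for posttest, 20 per arm is consistent. This stands, and it is why the point is that the 6-month number is unsupported and not that the calculation is wrong.

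**Discussion sentence.** Read with the sentences before it, it refers to dropout during training, so it agrees with the Sample size section. That also stands. The difficulty is that its conclusion about power is worded for the study as a whole.

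**Power.** A reader might infer that follow-up loss makes the trial underpowered, or that 16 per arm and sufficient power definitely fail for the three-visit analysis. The documents do not support that. They give no follow-up loss, and step 5 shows that loss of up to 20% changes none of the comparisons with 5, 12 and 32. Missing the 32 comes from averaging three sample sizes, which is a separate matter.

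**Trial status.** The figures of 39 recruited and 12 followed to 6 months are not a retention rate, since the number already due for that visit is not given.

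**Conclusion.** The point holds in limited form. The allowance covers the intervention period only and is exhausted at posttest; 16 per arm with all three visits requires zero loss over the following 6 months, and the article offers no basis for that. With an assumed 10–20% further loss, 14.4–12.8 per arm have complete data, and an effect with power 0.80 at 16 has about 0.75–0.68. Those power figures rest on three assumptions: the loss range, all three visits in the model, and complete-case handling. It is a gap in the support for the 6-month comparison, worth correcting because the remedy is cheap.

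**What to change.** Keep the total at 80 and make three changes.

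1. In the sample size section, state that the allowance secures 16 per arm at posttest only, and give the expected evaluable number at 6 months over 0–20% further loss (16.0, 15.2, 14.4, 13.6 and 12.8 per arm at 0, 5, 10, 15 and 20%). Retention pooled over arms among participants already due for the 6-month visit can inform the range.
2. In the Discussion, limit the sentence on dropout and sufficient power to posttest, to match.
3. Replace repeated measures ANOVA with a likelihood-based mixed model with group, visit and group-by-visit terms. Participants without the 6-month visit then still contribute their pretest and posttest data. The model assumes that data are missing at random, and it does not recover the 6-month values themselves.

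Cost: text edits and slightly more analysis work, with no extra participants. The stated precision at 6 months becomes less favourable. For comparison, keeping 16 complete cases per arm by recruitment alone would need 16/(0.80 × 0.90) = 22.2, so 23 per arm (92 in total), at 10% further loss, and 16/(0.80 × 0.80) = 25 per arm (100 in total) at 20%. That is not proposed.

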### Study design and procedures

This proposed study is a randomized controlled trial with pretest, posttest, and 6-month follow-up assessments (Fig. 1). The study protocol is approved by the Chang Gung University Institutional Review Board. Intervention therapists will screen for potential participants and obtain signed informed consents from the eligible individuals before they participate in the study. The enrolled participants will be randomly assigned into the COG, PE, SEQ, or DUAL group with the allocation ratio of 1:1:1:1 [31]. Random tables based on the type of recruitment site (day care centers versus nursing homes versus community) will be generated by an independent research assistant using the web-based Research Randomizer tool (freely available at http://www.randomizer.org/) [32]. The research assistant will use the random table to decide the group allocation of a newly enrolled participant and will inform the relevant therapist to carry out the respective intervention. The intervention therapist will not know the group allocation until the pretest measurement is completed. Each intervention group will consist of three to five participants and will be guided by a trained therapist. The participants will engage in 90 min of training, two to three times a week, for a total of 36 training sessions.

**Fig. 1 Fig1:**
[figure not shown]
Flow diagram of the study

Outcome measures, including cognitive functions, physical functions, ADLs, quality of life, and social participation, will be assessed before the treatment (pretest), after 36 training sessions (posttest), and 6 months after treatment (follow-up test). All outcome measures will be evaluated by independent evaluators who will be blinded to the group allocation of the participants. The evaluators will be trained by the principal investigator and senior therapists before the study begins to ensure that the measures will be conducted consistently. The assessments will be completed within 1 week before and after the intervention.

The first participant who adhered to the current study protocol was recruited in August 2015, although we piloted the study procedures in March 2015. We anticipate continuing to recruit until the sample size of 80 participants is reached.

### Interventions

The intervention therapists will be qualified occupational therapists or physical therapists, and will be trained by the principle investigator and the senior therapists to ensure standardized administration of the intervention protocols. The therapists will be required to complete a competency examination before providing the interventions. During the intervention period, the therapists will keep a daily log to record the progress and responses of each participant.

#### COG group

BrainHQ (Posit Science Inc., San Francisco, CA, USA) will be used to train different cognitive functions of the participants in the COG group. BrainHQ is a game-based computer program specifically designed to train various cognitive functions. This cerebral neuroplasticity-based computerized cognitive training program has been demonstrated to have significant benefits on various cognitive functions in community-dwelling older adults [33, 34]. During the training sessions, laptops with touchscreens will be provided to the participants so that they can play the computer-based games without having to manipulate a mouse. The BrainHQ games that involve cognitive functions of visuospatial processing, attention, memory, language, and logical thinking will be chosen for the participants to practice.

The participants will practice two to three games in 90 min, and the difficulty of the tasks will be adjusted to each individual's ability. The participants will not compete against each other but will play the games based on their own capability. The task will become more challenging as a participant improves. The intervention will contain 10 min of warm-up (explaining the rules), 70 min of cognitive training, and 10 min of cool-down (asking participants to recall and provide feedback to the activities). Each participant’s performance will be recorded in the daily log.

#### PE group

Previous studies suggested that a multimodal exercise program (aerobic with balance and strength training) may induce greater effects than a single mode of exercise [10, 35]. Therefore, we incorporate a multicomponent exercise program that includes balance training, strength training, and upper and lower limb aerobic exercise. The 90-min training session will be divided into two parts. In the first 45-min session, the participants will engage in aerobic exercise. The target intensity of the aerobic training will be 40 to 70 % of the maximal heart rate. Our pilot testing revealed that heart-related problems in some older people may prohibit them from achieving an aerobic level of exercise if measured by maximal heart rate. Thus, we will also adopt a Borg rating of perceived exertion (RPE) score of 12 to 14 as an indicator of achieving the aerobic level [36]. The therapists will adjust the aerobic level according to the capability of each participant, and the participants can rest as needed.

In the second 45-min session, the participants will engage in balance training and muscle strengthening. Static and dynamic balance training will be carried out under sitting and standing positions. Thera-Bands and weights will be used for the muscle-strengthening programs of the upper and lower limb muscles. The order of balance training and muscle strengthening will be intermixed. Each 45-min training session will contain 5 min of warm-up, 35 min of physical exercise, and 5 min of cool-down. The exercises will be performed without ergometers.

#### SEQ group

The participants in the SEQ group will first perform 45 min of physical exercise, followed by 45 min of cognitive training. During the physical exercise session, the participants will engage in 5 min of warm-up, 35 min of physical exercise, and 5 min of cool-down. The physical exercise programs will involve 15 to 17 min of aerobic exercise and 18 to 20 min of balance training and muscle strengthening. During the cognitive training session, the intervention therapists will spend 5 min explaining the rules of the tasks. Then, the participants will engage in 35 min of cognitive training with the BrainHQ games, as described in the COG group. The participants will be given one or two games to practice during the training session. The session will end with 5 min of cool-down activities such as proving feedback and asking the participants to recall the activities.

#### DUAL group

Participants in the DUAL group will be instructed to perform physical exercise and cognitive tasks simultaneously. Because dual-task training is a more challenging approach for participants with MCI, we have used PowerPoint presentations to design simpler versions of the BrainHQ games to make sure that the participants will be able to follow the instructions and engage in the games (Fig. 2). Similar to the COG and SEQ groups, the difficulty of the cognitive tasks will be adjusted as the participants improve in their performance. The physical exercises involved in this group will be carefully chosen to ensure that our participants can effectively perform the exercises while focusing on the cognitive tasks. The exercise programs will also include the components of aerobic exercise (e.g., stepping in place), balance training (e.g., static standing or walking), and muscle strengthening (e.g., using Thera-Band or weights). Examples of the dual-task training programs include practicing math calculations while stepping and search for a different bird on the screen (Fig. 2a) while strengthening the hip muscles with a Thera-Band.

**Fig. 2 Fig2:**
[figure not shown]
Examples of the PowerPoint versions of BrainHQ games. **a** Hawk eye: search for a different bird and determine the location of that bird. **b** Divided attention: determine whether the two figures have the same color, shape, or number

During the 90-min dual-task training session, the participants will engage in two combinations of physical activity and cognitive training program. For each combination, the intervention therapists will spend 10 min explaining the cognitive task and the method to perform the physical activity, followed by 35 min of training.

### Outcome measures

Sociodemographic variables, including age, gender, education level, comorbidity, smoking, alcohol intake, and depressive symptoms, will be recorded during the initial evaluation. This study will assess the participants before, immediately after, and 6 months after the intervention programs. The outcome measures will include several domains: cognitive functions, physical functions, ADLs, quality of life, and social participation.

#### Primary outcome measures

The MoCA will be used to assess general cognitive function. The MoCA examines visuospatial processing, naming, verbal fluency, abstract concept, short-term memory, digit forward and backward span, counting, and orientation. The total score for the MoCA is 30, with a higher number indicating a more intact cognitive function. The MoCA has been shown to be a valid and promising tool to detect MCI and early Alzheimer’s disease [37].

The color-naming Stroop test will be used to assess the abilities of inhibition, set-shifting, and selective attention [19]. The participants will be tested under congruent and incongruent conditions. In the congruent condition, the ink color of a word is consistent with the written color name; however, the ink color differs from the written color name under the incongruent condition. The participants will be required to read out the ink color of the word (but not the word itself) as accurately and as soon as possible. The time to complete the task will be calculated for each condition [38, 39].

